**Part II: Obstetric History**

1. Parity ………………………
2. Obstetric History

|  | Date  (Year) | Place  Home or HF* | GA** at delivery | Mode of  Delivery | Maternal  Complications | Neonatal  Outcome |
| --- | --- | --- | --- | --- | --- | --- |
| 1 |  |  |  |  |  |  |
| 2 |  |  |  |  |  |  |
| 3 |  |  |  |  |  |  |

*HF-Health Facility GA** Gestational age

1. ANC attendance Yes □ No □
2. If yes, facility attended: KNH □ Other facility □
3. Number of visits …………………………..
4. Date of first visit ./….../……..
5. Gestational age at first visit (in completed weeks) ………/40
6. Iron supplementation during pregnancy Yes □ No □
7. Duration of Iron supplementation…………
8. ANC Profile:

Haemoglobin (g/dl) ……………

Blood group: ………….. Rh: ……………

VDRL:

HIV:

**Part Ill: Index Admission**

1. Date of Admission ……/……./…….
2. Time of admission ……………….
3. Referral status

Referred from other facility □

Self referred □

Booked for delivery at KNH □

1. Gestational age at delivery (in completed weeks) ……../40
2. Gestational age calculated by Dates □ Quickening □

Ultrasound □ Fundal Height □

First clinic visit estimate □

1. Maternal Haemoglobin levels at admission ……………..
2. Maternal PCV at admission ………….
3. Maternal use of drugs for medical condition yes no
4. State which illness medication is used for in Q22 above.

**Part IV: Infant characteristics**

1. Gestational age (weeks)………………
2. Time of delivery …………
3. Time from admission to delivery (days)…………….. Or hours (if less than 24 hours)…………..
4. Live birth □ Still birth □
5. Admitted to NBU Yes □ No □
6. If Yes, diagnosis………………………………….
7. Sex of infant: Males □ Female □

1. Apgar score at 5 minutes

< 7 □ >7-10 □

1. Birth weight (g)…………………

1. Head circumference (cm)………………..
2. Neonatal haemoglobin at 24 hours of life:
3. Neonatal haematocrit at 24 hours of life:

**Part V: Follow up**

MATERNAL COMPLICATIONS

Post partum haemorrhage yes □ No □

Post partum anaemia Yes □ No □

Post partum sepsis Yes □ No □

NEONATE COMPLICATIONS

Clinical Jaundice Yes □ No □

Polycythemia Yes □ No □

Neonatal sepsis Yes □ No □

## APPENDIX IV: DATA AND MONITORING SAFETY PLAN

**Data and Safety Monitoring Plan**

Study Title: **THE EFFECT OF UMBILICAL CORD MILKING VERSUS DELAYED CORD CLAMPING ON SELECTED HAEMATOLOGICAL AND CLINICAL PARAMETERS IN PRETERM NEONATES AT KENYATTA NATIONAL HOSPITAL**

Principal Investigator: [name]

**BRIEF STUDY OVERVIEW**

**Objective**: To determine the effects of umbilical cord milking versus delayed umbilical cord clamping on haemoglobin and haematocrit level of pre term newborns.

**Methodology**: This will be a randomized controlled trial that will include mother-baby pairs at pre term gestation who meet the selection criteria, 140 newborns will be randomized to delayed umbilical cord clamping (≥60 seconds after delivery as the control group) and 140 newborns will be randomized to early umbilical cord milking (as the experiment group) and their haemoglobin and haematocrit level determined.

**DSMB OVERSIGHT RESPONSIBILITIES**

Oversight of the trial is provided by the DSMB.Meetings will take place to monitor on safety of patients and signals of efficacy, futility or harm. The DSMB members will have a first meeting before study is commenced. A meeting will be constituted in case of any adverse event and a final meeting on conclusion of the study. In case of unacceptable safety concerns/results occur, the board can recommend termination of the study. The safety of the participant is paramount.

**MONITORING PROCEDURES**

[name] will assure that informed consent is obtained prior to performing any research procedures, that all subjects meet eligibility criteria, and that the study is conducted according to the ERC-approved research plan.

Study data are accessible at all times for the PI to review. The PI will review study conduct every alternate day that is acquisition of consent, any dropouts, and completeness of questionnaire. The PI will review AEs individually real-time and in aggregate on a daily basis.

The PI will ensure all protocol deviations, AEs, and SAEs are reported to the ERC and KNH administration according to the applicable regulatory requirements.

**COLLECTION AND REPORTING OF SAEs AND AEs**

For this study, the following standard AE definitions are used:

**Adverse event:** Any unfavourable and unintended sign (including an abnormal laboratory finding), symptom or disease temporally associated with the use of a medical treatment or procedure, regardless of whether it is considered related to the medical treatment or procedure.

**Serious Adverse Event:** Any AE that results in any of the following outcomes:

- Death
- Life-threatening
- Event requiring inpatient hospitalization or prolongation of existing hospitalization
- Persistent or significant disability/incapacity

AEs are graded according to the following scale:

**Mild:** An experience that is transient, & requires no special treatment or intervention. This includes transient laboratory test alterations.

**Moderate:** An experience that is alleviated with simple therapeutic treatments. Includes laboratory test alterations indicating injury, but without long-term risk.

**Severe:** An experience that requires therapeutic intervention. If hospitalization (or prolongation of hospitalization) is required for treatment it becomes an SAE.

The study uses the following AE attribution scale:

**Not related:** The AE is clearly not related to the study procedures (i.e., another cause of the event is most plausible and/or a clinically plausible temporal sequence is inconsistent with the onset of the event).

**Possibly related:** An event that follows a reasonable temporal sequence from the initiation of study procedures, but that could readily have been produced by a number of other factors.

**Related:** The AE is clearly related to the study procedures.

**MANAGEMENT OF RISKS TO SUBJECTS**

Expected AEs

Expected AEs associated with the placental transfusion include:

MATERNAL- Postpartum haemorrhage (PPH)

NEONATAL- Polycythemia, Hyperbilirubinaemia and need for phototherapy

AE Management

**All adverse events will be reported to ERC within 24 hours.**

Maternal AE: To prevent PPH, AMTSL with administration of IM oxytocin will be included in all deliveries, labour ward is also equipped with other Uterotonics and a theatre in case PPH still occurs.

Midwives in labour ward are well trained to manage PPH.

Neonatal AE: The infant will be under continuous monitoring by the nurse and paediatrician in the respective wards. Kenyatta National Hospital is equipped to provide phototherapy for infants that require the intervention as well as if exchange transfusion is required.

**DATA ANALYSIS PLANS**

The statistician will not be blinded and data monitoring will be continuous, he will alert the principal investigator of any overt differences in the two groups. The study will be halted if there is evidence of significant statistical advantage in whichever group, to avoid denying the corresponding group an advantageous intervention.

In case of SAE, a report will be forwarded to ERC and study halted immediately pending clearance.

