# Study procedures

### PATIENT RECRUITMENT

Potential study participants will be recruited by the attending midwife at the triage area in labour ward as well as though the antenatal wards on a daily basis. The subjects are identified and chosen for the study if they meet the eligible criteria (inclusion and exclusion). Women will be enrolled at onset of spontaneous labour (cut off point <7 cm cervical dilation) if they are in labour or when the decision has been made for caesarean delivery for those not in labour. Recruitment and enrolment will be carried out by the research assistants, attending midwife or principal investigator who are all part of the study team.

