# DATA COLLECTION, MANAGEMENT AND ANALYSIS

After obtaining formal permission and ethical clearance, the study will be conducted at Kenyatta national hospital. The eligible participants will sign an informed consent. Respective data collection will be done in the Reproductive health labour ward, postnatal wards, paediatric wards and the neonatal ICU. Follow up data will be collected via phone call for the patients that have been discharged from hospital early.

Data will then be entered onto a REDCap electronic database with inbuilt consistency and range checks. No patient-identifiable information will be collected on the questionnaires or entered on to the REDCap database. The database will be password protected and only authorised personnel will have access to the data. The questionnaires will be stored in lockable cabinet and only the PI or the persons granted permission by the PI will have access. Automated haematology analyser will measure haemoglobin and haematocrit, by colorimetric principle.

The principal investigator and the recruited study research assistants will carry out the data collection. A structured survey questionnaire will be used to gather obstetrical and medical details and a venous blood sample will be taken from the neonate for laboratory investigations.

Training of research assistants will take place over the duration of one week; initially they will observe the process of obtaining informed consent and filling of the questionnaires. Thereafter they will work under supervision until the principal investigator is satisfied. The principal investigator will constantly review the questionnaires for completion. The intervention will be carried out by the midwife who will be trained by clinical tutorials and video tutorials.

The data monitoring will be continuous and the statistician will alert the principal investigator of any overt differences in the two groups. The study will be halted if there is evidence of significant statistical advantage in whichever group, to avoid denying the corresponding group an advantageous intervention.

LABORATORY PROCEDURES:

COLLECTION AND TRANSPORT:

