### Study discontinuation

The study's goal is to achieve ≥ 95% participant retention. So we will make every reasonable effort to retain any enrolled study participant to completion of the study. Participants are at will to withdraw from the study if they are unwilling or unable to comply with the required study procedures. In order to protect participants’ safety, the Principal investigator may withdraw study participants from the study.

A final evaluation will be completed for the study participants who withdraw from the study before completion. And the reasons for the withdrawal will be recorded in the participant’s records.

Finally the study may be discontinued at any time by the KNH-UoN-ERC.

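### Running between-arm differences are reported to the principal investigator, who shares in enrolment and data collection, instead of to the DSMB that holds the efficacy remit

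*Protocol*

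**What the plan says.** Two places in the Protocol set the reporting line. Under Data Collection, Management and Analysis, "the statistician will alert the principal investigator of any overt differences in the two groups". Appendix IV, Data Analysis Plans, repeats this ("he will alert the principal investigator of any overt differences in the two groups") and adds "The statistician will not be blinded and data monitoring will be continuous". Neither names another recipient.

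Appendix IV, DSMB Oversight Responsibilities, gives the comparative remit to a different body: "Meetings will take place to monitor on safety of patients and signals of efficacy, futility or harm". That section provides for a meeting before the start, one if an adverse event occurs, and one at the end.

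The principal investigator's other roles are:

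- Enrolment, shared: "Recruitment and enrolment will be carried out by the research assistants, attending midwife or principal investigator" (Patient Recruitment).
- Monitoring deliveries, shared with the research assistants and unblinded (Blinding).
- Data collection, shared: "The principal investigator and the recruited study research assistants will carry out the data collection". The same section has research assistants work under supervision until the principal investigator is satisfied.
- Data access: "Study data are accessible at all times for the PI to review" (Appendix IV, Monitoring Procedures).
- Withdrawal: "the Principal investigator may withdraw study participants from the study" (Study Discontinuation). The sentence opens by tying this to participant safety, and no criteria are listed.

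The Blinding section states blinding only for the laboratory staff who analyse the blood samples.

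**The concern.** Someone who attends a delivery cannot avoid knowing that infant's arm. Knowing which arm is ahead across the trial can be avoided, and it gives direction to any discretion that remains in how the trial is run. Here the only stated route for that knowledge ends at a person who takes part in enrolment and data collection and supervises those who share the work.

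Some outcomes leave room for judgement. Neonatal jaundice is a primary objective; it is examined by eye and, after early discharge, followed up by telephone on days three and seven. Maternal blood loss is an estimate. No assessor blinding is stated for either. Haemoglobin and haematocrit are measured by blinded staff on an automated analyser, so the assay is safe, but recruitment, retention and whether a 24-hour sample is obtained are not shielded in the same way.

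This is separate from the missing stopping boundary. Even with a sound boundary, an alert that fell short of it would still reach the principal investigator.

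**Working it through.** **1. The plan's own figure.** The point does not dispute the sample size, but the illustration uses it. With SD 2, difference 0.7, z-values 0.84 and 1.96, and 1:1 allocation:

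n = 2 × 2² × (0.84 + 1.96)² / 0.7² = 8 × 7.84 / 0.49 = 128 per arm.

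Adding 10% gives 256 × 1.1 = 281.6, against the stated 280, that is 140 per arm. The stated figure reproduces closely.

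**2. The passages side by side.**

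| Question | What the Protocol states |
|---|---|
| Who sees by-arm data as they accumulate? | The unblinded statistician, continuously |
| Who is told of a difference? | The principal investigator |
| Who is charged with efficacy, futility and harm signals? | The DSMB |
| When does the DSMB meet? | Before the start, on an adverse event, at the end |
| What sends by-arm results to the DSMB? | Nothing stated |

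The body with the remit has no stated feed, and the only stated feed goes elsewhere. This is an explicit instruction in the Protocol, given twice, so it is not a detail left for an analysis plan.

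**3. Illustration of sensitivity.** The inputs are 140 per arm (Protocol), a two-sided 5% test (Protocol), and the following assumptions, none of which is in the Protocol: no true difference in jaundice; a base rate of 20% to 50%; one alert at half enrolment (70 per arm) or three-quarters (105 per arm); and, after the alert, ascertainment 5 or 10 points higher in whichever arm already shows more jaundice. The final test is

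z = (p₁ − p₂) / √[p̄(1 − p̄) × 2/140], rejecting when |z| > 1.96.

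Only infants born after the alert are affected, so the shift in the arm's overall rate is diluted. At half enrolment, 5 points becomes 5 × 70/140 = 2.5 points, and 10 becomes 5. At three-quarters, 5 becomes 5 × 35/140 = 1.25 points, and 10 becomes 2.5. The shift also follows the arm already ahead, so it adds to a chance difference. Simulating 400,000 trials per cell gives these false-positive rates:

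| Alert at | Shift | Base 20% | 30% | 40% | 50% |
|---|---|---|---|---|---|
| Half | 5 points | 13.9% | 12.7% | 11.6% | 11.7% |
| Half | 10 points | 30.2% | 26.6% | 23.8% | 23.9% |
| Three-quarters | 5 points | 8.8% | 8.4% | 7.8% | 7.6% |
| Three-quarters | 10 points | 14.5% | 13.1% | 12.0% | 11.8% |

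With no shift the rate stays at about 5% throughout. The table shows how sensitive the jaundice comparison is to a modest change in recording that follows the trend. It does not predict that such a change would happen.

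**The case against.** The case on the other side is substantial and narrows the point.

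*The principal investigator does not personally judge most outcomes.* The midwife records blood loss (Maternal Data). A phlebotomist or paediatric resident draws the blood (Neonatal Data; Blood Samples), and blinded staff analyse it. Jaundice is examined with the paediatrician's help and entered by a research assistant (Clinical Jaundice). Nothing says that alerts are passed on to these people. This stands. A reader might infer that the recipient of the alert scores the outcomes, and the text does not support that. The route is indirect, through shared data collection and supervision of the assistants.

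*Withdrawal is limited.* A reader might infer a free hand to remove infants from the losing arm. Study Discontinuation ties withdrawal to safety, requires reasons to be recorded and a final evaluation to be completed, and sets a retention goal of at least 95%. The Abstract specifies intention to treat. Selecting infants by their 24-hour haemoglobin would mean discarding a measured primary outcome against that plan, so it is not a fair model of this risk. What remains is discretion without listed criteria.

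*A larger inflation is tempting.* Applying the same shifts to every infant in one fixed arm from the first birth gives 13-17% and 38-49% for base rates of 20-50%. An alert can affect only later infants, so those figures overstate this mechanism.

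*The DSMB is not barred from data.* Confidentiality permits release of study information for its monitoring, and Ethical Review mentions open DSMB reports. Both stand, but neither specifies by-arm reports during recruitment.

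*The identity key held only by the principal investigator* (Plan for Data Management) links families to codes. It does not link codes to arms, so it adds nothing here.

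*The principal investigator already sees all study data.* True, and for that reason redirecting the alert would not be enough by itself.

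**Conclusion.** The point holds as a governance fault with a plausible but unmeasured effect. The Protocol sends running between-arm differences to the principal investigator while giving efficacy, futility and harm signals to a DSMB with no stated by-arm feed and no interim efficacy meeting. The exposure lies in recruitment, retention, sample completeness and the recording of jaundice and estimated blood loss. It does not lie in the haemoglobin or haematocrit assay.

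Under the assumed 5- or 10-point shift, the 5% error for jaundice becomes about 12-14% or 24-30% with an alert at half enrolment, and about 8-9% or 12-15% at three-quarters. These figures rest on assumed base rates, shifts and alert times, and on the shift following the leading arm. The true effect could be nil. The change is worth making as a cheap improvement, because bias of this kind cannot be removed after the data are collected.

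**What to change.** - **Data Collection, Management and Analysis, and Appendix IV, Data Analysis Plans:** name the DSMB, in place of the principal investigator, as recipient of any between-arm difference.
- **Appendix IV, DSMB Oversight Responsibilities:** state that the DSMB receives these reports and may convene on them during recruitment. Without this, the redirected report has no meeting at which to be considered.
- **Appendix IV, Monitoring Procedures:** limit the principal investigator's review to consent, completeness, and adverse events seen individually or pooled over arms.
- **REDCap access:** set rights so that the principal investigator and research assistants cannot view or export outcomes by arm before database lock. The paper form in Appendix III carries the arm alongside the outcomes, so this restricts compiled comparisons and not knowledge of single cases.

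The cost is wording in four places and one access setting. The statistician and DSMB already exist. The downside is small: the DSMB takes on review during recruitment, and the principal investigator hears of a difference through the DSMB.

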**PLAN FOR DATA MANAGEMENT**

Compliance of regulatory documents and study data accuracy and completeness will be maintained through an internal study team quality assurance process.

Confidentiality throughout the trial is maintained by assigning a code to each participant, for purposes of identification. The key, linking the patient to the identifying code will be stored separately from the research data, in a password-protected database. This will only be accessible to the principal investigator.

## APPENDIX V: LINK LOG

**Study Title:** **THE EFFECT OF UMBILICAL CORD MILKING VERSUS DELAYED CORD CLAMPING ON SELECTED HAEMATOLOGICAL AND CLINICAL PARAMETERS IN PRETERM NEONATES AT KENYATTA NATIONAL HOSPITAL.**

| DATE | NAME | MOBILE NUMBER/  NEXT OF KIN NUMBER | ENROLLMENT IDENTIFICATION NUMBER |
| --- | --- | --- | --- |
| **1** |  |  |  |
| **2** |  |  |  |
| **3** |  |  |  |
| **4** |  |  |  |
| **5** |  |  |  |
| **6** |  |  |  |
| **7** |  |  |  |
| **8** |  |  |  |
| **9** |  |  |  |
| **10** |  |  |  |
